## Abstract

**Introduction:**

Coronary artery bypass grafting (CABG) via sternotomy remains the standard of care for multivessel coronary disease. Minimally invasive cardiac surgery for coronary artery bypass grafting (MICS-CABG) is an evolving technique with the potential to reduce surgical trauma and promote faster recovery without compromising outcomes. This protocol describes a pilot randomized controlled trial comparing MICS-CABG and conventional CABG in multivessel patients in a high-volume tertiary center.

**Methods and analysis:**

This is a single-center, prospective, randomized controlled pilot trial. A total of 100 patients with multivessel coronary artery disease will be randomized (1:1) to undergo either conventional CABG via median sternotomy or MICS-CABG through a left anterior thoracotomy. The sample size of 100 patients (50 per group) was defined based on feasibility and statistical precision. This allows estimation of an expected 8% major adverse cardiovascular and cerebrovascular events (MACCE) rate with a 95% confidence interval half-width of ±5% in each group. These data will inform sample size calculations for a future phase III trial. The primary outcomes are safety and feasibility. Feasibility will be assessed by the successful completion of the planned minimally invasive coronary revascularization strategy. Safety will be evaluated through the occurrence of MACCE within 30 days postoperatively. Secondary outcomes include operative time, mechanical ventilation time, conversion rate to sternotomy, bleeding volume, atrial fibrillation, postoperative ICU and hospital length of stay, and patient-reported quality of life (EQ-5D-5L) 6 months postoperatively. The trial is ongoing at this moment.

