## 8. Sample size and statistical analysis

This is a pilot, exploratory randomized study comparing two surgical strategies (MICS vs. conventional CABG). The primary objective is to obtain descriptive estimates of event rates (rather than on hypothesis testing), between-group differences, and variability of outcomes to guide the design of a subsequent phase III trial.

The sample size of 100 patients (50 per group) was determined by operational feasibility and expected precision, rather than hypothesis testing. Assuming a conservative 8% 30-day MACCE rate (consistent with the average reported for conventional CABG in the 2025 ESC/EACTS Guidelines) the 95% confidence interval (Wilson) has a half-width of approximately ±5% in the overall cohort and ±7–8% per arm.

This approach aligns with published pilot trials in hybrid or minimally invasive CABG, which typically include 80–120 participants and use similar precision-based rationales.

Categorical variables will be presented as frequencies and percentages, and compared using the Chi-square or Fisher’s exact test, as appropriate. Continuous variables will be expressed as mean ± standard deviation or median (interquartile range) and compared using the Student’s t-test or Wilcoxon rank-sum test. Time-to-event outcomes (e.g., MACCE-free survival) will be analyzed using the Kaplan-Meier method.

No imputation for missing data will be performed, as this is a pilot trial focused on descriptive analyses rather than formal hypothesis testing. Missing data will be reported transparently, and analyses will be conducted using available cases.

All analyses will be performed according to the intention-to-treat principle. Participants randomized to the minimally invasive CABG group who require conversion to full sternotomy will remain in the MICS CABG arm for all primary and secondary outcome analyses. Conversion events will be reported descriptively, including their timing and reasons.

The decision to use or avoid cardiopulmonary bypass (on-pump or off-pump) will be left to the operating surgeon, according to intraoperative findings.

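### The abstract states ±5% precision for MACCE in each group, but 50 patients per group give about ±8 points; ±5% belongs only to the pooled 100, as Section 8 says

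*Protocol article*

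**What the plan says.** The Methods and analysis part of the abstract gives the basis of the sample size: "The sample size of 100 patients (50 per group) was defined based on feasibility and statistical precision". Taking 8% as the anticipated MACCE frequency, it then puts the resulting precision at a "95% confidence interval half-width of ±5% in each group". It adds that the data will feed the sample size calculation of a later phase III trial.

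Section 8 (Sample size and statistical analysis) starts from the same assumption, "Assuming a conservative 8% 30-day MACCE rate", and the same 50 per group. It names the Wilson method for the 95% interval and says that it "has a half-width of approximately ±5% in the overall cohort and ±7–8% per arm".

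**The concern.** The design, event rate and confidence level are the same in both places, but the per-group precision differs: ±5% in the abstract, ±7–8% in Section 8. The ±5% appears in both, attached to each group in one and to the two groups combined in the other.

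The figure describes how well the trial can estimate its primary safety outcome as the abstract defines it, 30-day MACCE. Someone who reads only the abstract would expect a per-arm interval of roughly 3% to 13% around an 8% rate. If the abstract is wrong, that reader, who may be planning the phase III trial, expects a much tighter safety estimate than 50 patients can give. Most of the shortfall is on the upper side, which matters most for safety.

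**Working it through.** **Inputs.** Event rate p = 0.08 (abstract and Section 8). n = 50 per group and 100 in total (both). Two-sided 95% level, z = 1.96 (both). Wilson interval (Section 8). The expected counts are 0.08 × 50 = 4 and 0.08 × 100 = 8.

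**Formulas.**
- Wald half-width: z × √[p(1 − p)/n]
- Wilson centre: (p + z²/2n) / (1 + z²/n)
- Wilson half-width: z × √[p(1 − p)/n + z²/4n²] / (1 + z²/n)

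**Step 1: reproduce Section 8.**
- Pooled, n = 100. Wilson half-width = 1.96 × √(0.000736 + 0.000096) / 1.0384 = 0.0544. The centre is 0.0955, so the interval is 4.1% to 15.0%. Wald gives 0.0532. This agrees with Section 8's rounded ±5% for the overall cohort.
- Per arm, n = 50. Wilson half-width = 1.96 × √(0.001472 + 0.000384) / 1.0768 = 0.0784. The centre is 0.1100, so the interval is 3.2% to 18.8%. Wald gives 0.0752. This agrees with Section 8's ±7–8% per arm.

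**Step 2: try to reproduce the abstract's ±5% at n = 50.** The abstract names no interval method, so several were tried at 4/50.

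| Method | Half-width (points) |
|---|---|
| Wald, 95% | 7.5 |
| Jeffreys, 95% | 7.6 |
| Wilson, 95% | 7.8 |
| Agresti–Coull, 95% | 8.4 |
| Clopper–Pearson, 95% | 8.5 |
| Wald with continuity correction, 95% | 8.5 |
| Wald, 90% two-sided (same z as 95% one-sided) | 6.3 |
| Wald, 80% two-sided | 4.9 |

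No 95% method comes near 5 points. Only an 80% interval does, and the abstract says 95%.

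**Step 3: group size that would make the abstract true.** Wald: n = 1.96² × 0.08 × 0.92 / 0.05² = 113.1, so 114 per arm. Wilson: the smallest n with a half-width of at most 0.05 is 118 per arm. Both are more than twice the planned 50 (114/50 = 2.3; 118/50 = 2.4).

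**Step 4: context only, the between-group difference.** With 4/50 in both arms, the Newcombe half-width is √[(0.0800 − 0.0315)² + (0.1884 − 0.0800)²] = √(0.00235 + 0.01175) = 0.119, or about ±12 points.

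**The case against.** The strongest reply is that the section governing the design is already correct. Section 8 names the interval method, separates pooled from per-arm precision and gives the right range for each. No decision rule, threshold or analysis depends on the abstract's ±5%. That is true, and it makes this an error of reporting, not of design. It does not rescue the sentence: a abstract is often read alone, and this one states a figure that no 95% method gives with 50 patients.

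A reader might infer more than the document supports:

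- *That the sample size loses its justification or must grow.* It does not. Both the abstract and Section 8 cite feasibility beside precision ("The sample size of 100 patients (50 per group) was determined by operational feasibility and expected precision"). Section 8 also compares the size with pilot trials of 80–120 participants, and the strengths and limitations list in Section 9 calls the size feasibility-driven. The 114 to 118 per arm shows how far off the abstract is; it is not a target for this trial.
- *That Section 8 is also wrong because it quotes a pooled figure.* It labels that figure as the overall cohort, and 5.3 to 5.4 points is fairly rounded to about 5.
- *That the ± sign is an error because the Wilson interval is skewed around 8%.* A half-width is a legitimate summary of an interval's width. Giving the upper limit would help, but leaving it out is not a mistake.
- *That the precision of the between-group difference is wrongly missing.* Section 8 does list such differences among the quantities to be described. But the sample size was set "rather than hypothesis testing", the comparison of techniques sits under the secondary objectives, and a condensed article need not give precision for every quantity.

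**Conclusion.** The abstract is wrong as written, and Section 8 is right. At an 8% rate with 50 patients, the 95% half-width is 7.8 points (Wilson) or 7.5 (Wald), not 5. The abstract's figure is therefore about a third too small (5/7.8 = 0.64). The Wilson upper limit is 18.8%, which is 10.8 points above the assumed rate and 5.8 points above the 13% that the abstract's ± implies. The ±5% is the precision of the two arms combined.

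This rests on the protocol's own 8% rate, with 4 events observed in 50 and all 50 patients in each arm contributing. The conclusion does not depend on the choice among the usual 95% methods. It does not extend to the sample size, to the planned analyses or to Section 8's figures, all of which stand.

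**What to change.** In the abstract, replace the precision statement with: about ±8 percentage points in each group (4/50: Wilson 95% CI 3.2% to 18.8%) and about ±5 points in the overall cohort. The abstract and Section 8 then agree.

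Optionally, Section 8 could add the per-arm interval with its upper limit, and the precision of the between-group difference: about ±12 points (Newcombe, at 4/50 versus 4/50). These would help phase III planning but are not corrections.

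The cost is wording only. No patients are added and no analysis changes; the precision stated in the abstract becomes less favourable.

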**Ethics and dissemination:**

The protocol was approved by the Institutional Research Ethics Committee under que number CAAE: 54175921.8.0000.0068. Results will be disseminated through peer-reviewed publications and scientific conferences.

**Trial registration number:**

ClinicalTrials.gov NCT06794359.

## 1. Introduction

### 1.1. Background

Minimally invasive surgery has been a breakthrough in medicine, especially in more developed countries. It represents an evolution of current techniques associated with new technologic devices, that allow a safe and effective procedure associated to an aesthetic benefit.

Invasive treatment of coronary artery disease has been on a plateau lately. Percutaneous treatment that emerged as a promise to replace surgical methods, has already shown its limitations, even with the use of drug-eluting stents. Traditional CABG (coronary artery bypass grafting surgery), which has been considered the gold standard, has been criticized for its high degree of invasiveness.

Based on this precept, interest has emerged in creating a surgical approach that causes less trauma [1]. Surgical access using minimally invasive incisions are gaining space and have shown less postoperative pain, shorter hospital stays, earlier mobilization and functional recovery, in addition to reducing the costs of the procedure [2]. Recent randomized studies such as the ongoing MIST trial have further explored these patient-centered benefits, focusing on postoperative quality of life and recovery after minimally invasive coronary surgery [3].

Cardiac surgery has some challenges that are beyond other specialties. The heart is a vital organ with intrinsic chronotropism that lies inside a rigid rib cage.

Specifically in CABG, the thin caliber of the coronaries and their distribution throughout the cardiac territories creates even a greater challenge. However, new surgical techniques associated with new devices, demonstrated the viability of complete revascularization through a limited access incision.

In an attempt to minimize surgical trauma and the morbidities caused by conventional median sternotomy and the use of On Pump surgery, some alternatives have emerged with promising results.

Among those efforts, we can highlight the beginning of the coronary artery grafting surgery without the use of cardiopulmonary bypass (Off Pump CABG), followed by hybrid revascularization, minimally invasive surgery by lateral thoracotomy under direct vision, partially assisted robot surgery and fully endoscopic surgery with using robots [4].

In 1996, Calafiore published a series successfully operated on cases where CABG was performed Off Pump through the left lateral thoracotomy access. In this series, the left internal mammary artery (LIMA) was partially dissected and anastomosed to the anterior descending artery [5].

### 1.2. Historical experience in our institution

At our institution, the left mini-lateral thoracotomy and other minimally invasive access have been used in several cases to perform CABG, during its history.

In a series of 43 cases, Jatene proved that it was possible to dissect the LIMA in its full extension guided by video thoracoscope inserted through the main incision, followed by Off Pump CABG [6].

In another series of 120 cases operated on our institution and published in early 2000’s, Oliveira et al performed the treatment of single vessel coronary disease through mini access. Mortality rate was 0.8%. The conversion rate to median sternotomy was 4.2%. In an angiographic re-study foreseen in the study, the patency of the left internal thoracic artery was 98%. After 24 months of follow-up, event-free survival was 94.9% [7].

In a recent publication, 60 patients were randomized to treatment by conventional CABG surgery or by the hybrid myocardial revascularization approach. In the hybrid group, 40 patients underwent revascularization of the left anterior descending artery (LAD) using the left internal thoracic artery, using a median mini sternotomy access [8].

Currently, minimally invasive surgery though mini lateral thoracotomy is the most common technique used. Initially it was used only for the treatment of the LAD, but technology advances and surgical improvement allowed complete revascularization under direct vision.

It is possible to perform the dissection of the internal thoracic arteries in all their extension, in addition to allowing direct anastomosis of the grafts in the aorta. The method allows good visualization of the coronary arteries, especially on the left side of the heart and the posterior descending branch of the right coronary.

This current approach does not require infrastructure other than that usually offered in surgeries and is accessible to all cardiovascular surgeons. The investment to perform the surgery consists of permanent surgical material, associated with the disposable stabilizers offered by the industry [9].

In a published series of 450 minimally invasive CABG Off Pump cases, the rate of complete revascularization was 95%, with a mortality rate of 1.3%. The conversion rate to median sternotomy was 3.8% and the necessity of cardiopulmonary bypass (CPB) assist in 7.6%. The average hospital stay was 4 days [9].

Off Pump heart exposure can be challenging especially in more complex cases and during surgeon’s initial experience. In those cases, peripheral circulatory assistance for hemodynamic support, without the need for aortic cross clamping, is encouraged by experienced authors [10,11].

Off Pump graft patency in MICS CABG cases was proven to be satisfying after 6 months from surgery, with 100% LIMA to LAD patency and 92% overall graft patency [12].

Additionally, great outcomes were also published in MICS CABG using CPB with peripheral canulation, aortic cross clamping and blood cardioplegia. Complete revascularization with a mean of 3 grafts per patient and low mortality were reported in a series of 170 consecutive patients [13].

To achieve good performance, especially in initial experience, patient selection must be reasonable, choosing patients with preserved left ventricle function, feasible coronary anatomy, non-obese and without thorax deformities.

Although the 2018 ESC/EACTS guidelines on myocardial revascularization provide a IIa recommendation for minimally invasive CABG in isolated LAD lesions, it does not endorse its routine in multivessel disease once most publications are series of cases and initial centers experiences [14].

However, more recent evidence has challenged this limitation. A large systematic review encompassing approximately 7,500 patients undergoing MICS-CABG for multivessel disease demonstrated the feasibility and safety of the approach, with a high rate of complete revascularization (average of 2.8 grafts per patient) and low perioperative mortality [15].

In line with these findings, a propensity score–matched retrospective study compared minimally invasive CABG with conventional sternotomy CABG in patients with multivessel coronary disease. The authors reported comparable completeness of revascularization, graft patency, and long-term clinical outcomes between groups, with 5-year rates of MACCE and mortality remaining similar [16].

### 1.3. Rationale for the study

Minimally invasive coronary artery bypass grafting (MICS-CABG) through a left mini-thoracotomy has evolved from isolated LAD procedures to complete multivessel revascularization with excellent results in selected case series. Despite its growing adoption, the evidence supporting MICS-CABG remains largely based on single-center, non-randomized studies, limiting guideline endorsement for multivessel disease.

Recent reviews have summarized the current evidence base for minimally invasive coronary surgery, highlighting that, although MICS-CABG enables multivessel revascularization through a mini-thoracotomy without cardiopulmonary bypass, its widespread adoption remains limited because most available data come from single-center observational series. The authors emphasized that only two randomized controlled trials are currently ongoing, both led by highly experienced surgeons in high-volume centers, which may limit generalizability to the broader surgical community [17].

The MINI-CABG trial was therefore designed as a pragmatic, pilot randomized controlled study comparing MICS-CABG with conventional open CABG under contemporary surgical standards. Conducted in a South American tertiary center by surgeons undergoing structured training and progression in the minimally invasive technique, this trial aims to provide prospective, controlled data reflecting real-world conditions and to inform the design of a future large-scale phase III study.

### 1.4. MICS-CABG advantages

Less surgical traumaLower wound infection rates and mediastinitisLower rates of blood transfusionEarlier patient mobilization in ICUShorter hospital stay and faster recovery to daily activities

### 1.5. Disadvantages in MICS-CABG

Median sternotomy conversion riskCardiopulmonary pump through femoral cannulation and its peripherical inherent risksPossible longer CPB times and aortic cross clamp timesWhen Off Pump technique is chosen, direct access to the right coronary artery becomes more challenging, although its distal branches are possible to treat.

Most of those disadvantages are related to the surgeon’s and center’s learning curves. They are usually minimized with the mastery of this new technique and a broader clinical application.

## 2. Objectives

### 2.1. Primary objective

To evaluate the feasibility and safety of performing coronary artery bypass grafting through a minimally invasive left anterior thoracotomy approach.

### 2.2. Secondary objectives

To explore differences in operative performance, postoperative recovery, complication rates, and patient-reported outcomes between minimally invasive and conventional CABG techniques.

## 3. Methods and analysis

### 3.1. Study design

This is a single-center, prospective, randomized controlled pilot trial, conducted over 30 months. A total of 100 patients will be randomized to undergo either to minimally invasive CABG through left anterior thoracotomy in the 4^th^ or 5^th^ intercostal space or conventional median sternotomy CABG. The use of CPB will be at the discreet of the surgeon.

Patients will be randomized in a 1:1 ratio using variable block sizes (blocks of 4–8), generated and managed electronically within the REDCap platform. This method ensures balance between groups while minimizing the predictability of the next allocation. The randomization module was configured by an independent researcher not involved in patient enrollment or surgery. Participants will only be randomized after meeting all eligibility criteria and signing the informed consent form.

All patients will be operated on by the same surgical team, with the standardized technique, at a high-volume tertiary cardiac surgery center.

Informed consent approved by our institutional research and ethics in committee under the number CAAE: 54175921.8.0000.0068, will be applied to all participants prior to surgery.

Post-operative follow up will be of 6 months. The postoperative evaluations will be divided into an outpatient presential evaluation around 1 month from discharge, followed by telephone contact 6 months. Follow up maybe extended up to 2 years after the surgery by telephone contact, to collect descriptive mid-term data, depending on institutional feasibility and patient availability.

This protocol follows the SPIRIT 2013 guidelines for randomized clinical trial protocols. The SPIRIT schedule of enrolment, interventions, and assessments is shown in Fig 1.

**Fig 1 pone.0337829.g001:**
[figure not shown]
SPIRIT schedule of enrolment, interventinos, and assessments for the MINI CABG trial.

### 3.2. Study status and timeline

The MINI-CABG trial began recruitment in October 2023. As of August 2025, a total of 60 patients have been enrolled and completed surgery, of whom 50 have completed the 6-month follow-up. Recruitment is ongoing, with an estimated total enrollment of 100 patients expected to be completed by June 2026. Data collection, including the planned follow-up period, is anticipated to be completed by January 2027. No study results have yet been generated or analyzed.

### 3.3. Ethics and dissemination

This study was approved by the Institutional Review Board of the Hospital das Clínicas, University of São Paulo (Comitê de Ética em Pesquisa do HCFMUSP – CAAE: 54175921.8.0000.0068). All participants provided written informed consent prior to enrollment. The study adheres to the principles outlined in the Declaration of Helsinki. Results will be published in peer-reviewed journals and presented at conferences.

The trial has been registered at ClinicalTrials.gov under the registration number NCT06794359.

The study received full ethics approval before patient enrollment and was registered retrospectively at ClinicalTrials.gov in October 2024, due to administrative and institutional delays during the trial initiation phase. However, we emphasize that all data have been collected prospectively, according to the predefined protocol. No outcomes were analyzed or reported prior to registration. All outcomes will be analyzed only after all patients have completed their follow-up.

This study is supported by a public grant from the São Paulo Research Foundation (FAPESP; grant 2021/11947–5). The trial also received non-financial technical collaboration from Medtronic (technical assistance and materials), without acting as a sponsor or participating in study design, data analysis, or manuscript preparation.

